**Methods:**

A cluster randomized controlled trial will be conducted in northwest Ethiopia to determine the effectiveness of integrating traditional care with modern TB care. The intervention will be conducted in randomly selected districts in the South Gondar Zone. The control group will be an equal number of districts with usual care. The intervention comprised three key components, which include referral linkage from traditional to modern health care; training of health professionals and traditional care providers in three different rounds to increase their knowledge, attitude, and skills toward the referral systems; and TB screening at traditional health care sites. The primary outcomes of interest will be an increase in case detection rate, and the secondary outcomes of interest will be decreased diagnosis delays and catastrophic costs for TB patients. Data will be collected in both the intervention and control groups on the main outcome of interest and a wide range of independent variables. Generalized linear mixed models will be used to compare the outcome of interest between the trial arms, with adjustment for baseline differences.

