### Study design and participants

A parallel group cluster randomized controlled trial with two arms (i.e., intervention and control arms) will be conducted in six districts of the South Gondar Zone. The outcome of interest will be case detection rate, diagnosis delay, and catastrophic costs. The control arm will include the routine standard TB cares. In the intervention arm, TB-suspected individuals (i.e., people with coughs for more than 2 weeks, fever, chills, night sweats, anorexia, weight loss, chest pain, hemoptysis, lymphadenopathy, fatigue, or growth failure in children) will be identified by the traditional healer in traditional care centers (traditional healer clinics, holy water, mosques) and referred to modern health care centers (health facilities) where there is TB diagnostic service.

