### Randomization and recruitment

Randomization will be done at the district level. There are thirteen districts and two town administrations. Among a total of districts and town administrations, six districts and/or town administrations in South Gondar Zone will be selected using the random.org software by considering the rule of thumb assumption that covers 40% of districts and town administrations. Thus, the selected districts/town administrations will be assigned to the intervention and control arms with a 1:1 allocation ratio. This means three districts or town administrations will be randomly assigned to the intervention arm, and the other three districts or town administrations will be assigned to the control arm. District or town size will not be considered in the randomization process. All health facilities in the intervention and control arms fulfilling the eligibility criteria will be included in the study. The eligibility criteria for the inclusion and/or exclusion of health facilities will be based on the availability of TB diagnostic and treatment services, including the microscope diagnostic service and DOT programs. Participants will recruit to the study when confirmed they have any form of TB and are registered to the DOT programs. Participants will enter into the trial individually based, and patients will recruit continuously until the desired sample size achieve. Recruitment of participants will be from July 1 to September 30, 2022. The statistician who allocated the intervention and control arms, an expert who assesses the outcomes, participants who will be assigned to intervention and control arms, and healthcare providers who provide TB care will not be aware of who were assigned to the intervention and control arms. The project manager and/or investigators will be unblinded.

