#### Sample size calculation for TB detection rate

Since the case detection rate will be calculated by considering the WHO estimator for the year 2023 per 100,000 populations. Estimating the number of TB cases for that year will be computed by using total cases in the year/100,100 * total population found in the catchment area multiplied by 100, expressed as a percentage. Therefore, all cases that are confirmed as TB patients in the selected districts will be considered as the final sample size.

The number of clusters involved in the study was determined using the following formula [39]: The number of clusters (*K*) required in each arm for unequal cluster sizes was also determined using the formula [40]: *K* = *n* [1 + ((CoV2 + 1) *m* − 1) ICC]/*m*′], where Cov2 = coefficient of variation of 0.25, effective ICC value of 0.03 for cluster-level ICC value of TB detection rate, *n* = sample size under individual randomization, *m* = average number of individuals found in each cluster was 18. From 40 clusters, with unequal clusters for intervention and control arms, 24 clusters included in the intervention, and 16 clusters in the control arm.

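### The sample-size statement for the primary outcome counts 40 clusters split 24:16, but the trial randomises six districts, three per arm, so the calculation does not describe the randomised design.

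*Protocol article*

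**What the plan says.** All references are to the protocol article.

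- Study design and participants: the trial "will be conducted in six districts of the South Gondar Zone".
- Randomization and recruitment: "Randomization will be done at the district level"; "six districts and/or town administrations in South Gondar Zone will be selected using the random.org software"; these are then "assigned to the intervention and control arms with a 1:1 allocation ratio", so that "three districts or town administrations will be randomly assigned to the intervention arm" and three to control. All eligible health facilities in the selected areas are included; nothing says that facilities are randomised.
- Abstract, Methods: "The control group will be an equal number of districts with usual care".
- Outcomes of interest: case detection rate is the primary outcome.
- Sample size calculation for TB detection rate: a formula for the number of clusters K required in each arm with unequal cluster sizes, "where Cov2 = coefficient of variation of 0.25, effective ICC value of 0.03 for cluster-level ICC value of TB detection rate", and an average of 18 individuals per cluster. It ends: "From 40 clusters, with unequal clusters for intervention and control arms, 24 clusters included in the intervention, and 16 clusters in the control arm". The section does not say what these clusters are, and gives neither n under individual randomisation nor a target difference for detection rate.
- The sample-size sections for diagnosis delay and for cost describe the study as multicentre and individually randomised, which is a third description of the design.

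**The concern.** K in a cluster sample-size formula counts independently allocated units. The article has six of these in equal arms, yet the only cluster calculation for its primary outcome ends with 40 in unequal arms. Neither the total nor the split fits the randomisation section.

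If the 40 are sites inside the six districts, the calculation leaves out variation between districts. It also ignores that the arm comparison rests on six units, which is 4 degrees of freedom. The primary outcome then has no precision statement that applies to the trial being run. An analysis that followed the 40 as its clusters would give standard errors that are too small.

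**Working it through.** **Inputs.** From the detection-rate section: m = 18, ICC = 0.03, and 0.25 for variation in cluster size, which can be read as CoV = 0.25 (CoV² = 0.0625) or as CoV² = 0.25. No n is given there. As an assumption, n is borrowed from the secondary outcomes:

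- Delay, 59.9% v 45.9%: 199 per arm before non-response (199 × 2 × 1.10 = 438, as stated); final 208 per arm.
- Cost, 40% v 27%: 206 per arm before non-response (206 × 2 × 1.10 = 453, as stated; 453/2 = 226.5); final 214 per arm.

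**Reproducing the 40.** K per arm = n[1 + ((CoV² + 1)m − 1)ICC]/m. The bracket is the design effect:

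- CoV² = 0.0625: 1 + (1.0625 × 18 − 1) × 0.03 = 1.544
- CoV² = 0.25: 1 + (1.25 × 18 − 1) × 0.03 = 1.645

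| n per arm | K at 1.544 (rounded up) | K at 1.645 (rounded up) |
|---|---|---|
| 199 | 17.07 (18) | 18.19 (19) |
| 206 | 17.67 (18) | 18.83 (19) |
| 208 | 17.84 (18) | 19.01 (20) |
| 214 | 18.35 (19) | 19.56 (20) |
| 226.5 | 19.43 (20) | 20.70 (21) |

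The formula thus asks for 18 to 21 per arm. Twenty per arm, 40 in total, is reached with n = 208 or 214 and CoV² = 0.25, or with n = 226.5 and CoV = 0.25. So the total can be reproduced, but only with a borrowed n and with equal arms. The 24:16 split does not come out of the formula.

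**Against the randomised units.** Six districts, three per arm: 40/6 = 6.67.

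**Could larger clusters make three per arm enough?** Districts hold more than 18 patients, so K must be recomputed. With the cost total of 428 patients in six districts, m = 71.3:

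- CoV² = 0.0625: design effect 3.24, K = 214 × 3.24/71.3 = 9.7, so 10 per arm
- CoV² = 0.25: design effect 3.65, K = 10.9, so 11 per arm

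In general K = n(1 − ICC)/m + n × ICC × (1 + CoV²). As m grows, the first term vanishes and the second is a floor. At ICC 0.03 the floor runs from 199 × 0.03 × 1.0625 = 6.3 to 226.5 × 0.03 × 1.25 = 8.5 per arm, so three is never enough. The floor falls to three only if the district-level ICC is 3/[n(1 + CoV²)], that is 3/(226.5 × 1.25) = 0.011 to 3/(199 × 1.0625) = 0.014. The formula makes no allowance for 4 degrees of freedom, where the two-sided 5% critical value is 2.78 rather than 1.96.

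**Illustration on the rate scale.** Assumptions: 2.6 million/15 = 173,000 people per district; 132 per 100,000; control detection 61% (the regional 39% not diagnosed or not reported, from the Background); between-district CV 0.10 to 0.25, for which the article gives no value; no gain from baseline adjustment. The standard formula for comparing cluster rates, with three clusters per arm and 80% power, gives these detectable ratios:

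- CV 0.10: 1.43, so detection must rise to 0.61 × 1.43 = 87%
- CV 0.15: 1.63, so 99%
- CV 0.25: 2.26, so above 100%

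**The case against.** The best defence is that the 40 are health facilities nested in the six districts. The setting section lists 96 health centres and more than 10 hospitals over 15 areas, and (96 + 10)/15 × 6 = 42.4 is close to 40. Unequal numbers of facilities per arm would then be natural under a 1:1 allocation of districts. That may explain where the figures come from, but it does not rescue the calculation, because facilities inherit their district's arm.

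Several stronger readings are tempting and are not supported:

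- That the 40 can only be facilities. The article does not define them, it also mentions kebeles, health posts and traditional care sites, and 42.4 assumes an even spread with no eligibility filter. Most plausibly facilities is as far as the text goes.
- That 16 control clusters fall short of the formula's own requirement. The requirement rests on a borrowed n, and 24:16 is as efficient as 2/(1/24 + 1/16) = 19.2 per arm, about 4% below 20.
- That 40 × 18 = 720 should equal 416 or 428. Those totals serve delay and cost; for detection rate the article takes all confirmed cases in the selected districts.
- That the analysis is bound to use facilities as clusters. The Data analysis section refers to randomly selected clusters, which fits districts better than facilities.
- That the trial cannot detect a realistic change. The detectable rates depend on assumed CVs, and the planned baseline adjustment could reduce between-district variation.

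**Conclusion.** The detection-rate sample-size statement is wrong as written. It contradicts the allocation in both number (40 against 6, a factor of 6.7) and balance (24:16 against 3:3), and it is the only such statement for the primary outcome. This follows from the text alone.

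The size of the precision loss is conditional. With a borrowed n, the formula wants 18 to 21 clusters per arm at m = 18. With ICC 0.03 carried to district level, it wants more than six per arm at any district size, against three. A district-level ICC below about 0.011 to 0.014 would remove that floor, so the result should not be put more strongly than its assumption. The detectable rates are illustrations only.

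**What to change.** 1. State that the randomised cluster is the district or town administration: six in total, three per arm.
2. Define the 40 units and relabel them as sub-units within districts, or delete 40, 24 and 16 as the cluster count.
3. Restate the detectable change in case detection rate for three versus three districts, using between-district variation from the planned baseline data and small-sample degrees of freedom. State the n or target effect, and whether 0.25 is CoV or CoV².
4. Name the district as the cluster in the analysis.
5. Reconcile the individually randomised wording in the delay and cost sample-size sections with district randomisation.

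The cost is recalculation, rewording and a less favourable stated precision. No extra clusters or patients are asked for.

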### Data collection

Data will be collected on the dependent variables (i.e., case detection, diagnosis delay, and cost of TB care) and independent variables (i.e., socio-demographic, health-seeking behavior variables, patient knowledge of TB, healthcare accessibility, distance, contact history, and support). Secondary data will be collected from the patient’s medical records, and primary data will be collected using a structured questionnaire adapted from previous literature. The structured questionnaire is composed of socio-demographic and economic factors, health-seeking behaviors, patient knowledge, service accessibility, stigma, contact history, the catastrophic cost of TB, diagnosis delay, and healthcare initiation. The questionnaire will be translated into the national language (Amharic) spoken by almost all residents in the study area. The data will be collected using face-to-face interview questionnaires. The data will be collected by BSc nurses or public health officers who had data collection experience. Nurses or public health officers who had MSc/MPH degrees will be selected for data collector supervisors. The data will be collected at baseline and at the end of 1 year of the intervention.

### Measurements

The case detection rate will be calculated as the number of cases notified divided by the number of cases estimated for that year, expressed as a percentage [41]. The WHO estimator for the year 2022 was 132 per 100,000. Estimating the number of TB cases for that year will be computed by using that year/100,100 * total population of the catchment area. Estimating the number of TB cases for that year will be computed by using total cases in the year/100,100 * total population found in the catchment area multiplied by 100, expressed as a percentage.

Patient costs and their annual incomes collected in Ethiopian birr will be converted to US dollars ($) with an average exchange rate for the dates during which data collection took place. The total costs will be considered the sum of the entire direct and indirect costs of TB illness to patients. Out-of-pocket payment for health care (medical) will be the direct payment made for medical care directly by individuals at the time of service using minus insurance reimbursement. Out-of-pocket costs will be a payment for formal medical services, informal traditional practitioners, clinics, health centers, pharmacies, and hospitals for medical services and products such as diagnosis, treatment, and medicine. Out-of-pocket payment net will be a total out-of-pocket payment (medical and non-medical) minus any reimbursement received for payments made. The direct costs will be calculated by the sum of any payment affected by medical and non-medical costs. The medical costs will be the sum of out-of-pocket payments for TB diagnosis and treatment made by TB patients in a given household buying medicines, payments for diagnostic tests, and net reimbursements. The direct non-medical costs were out-of-pocket payments for transport, accommodation, and food before and during TB diagnosis. An indirect cost is costs incurred as a result of TB healthcare seeking and hospitalization, during the TB episode. The total period of absence (in hours) will be multiplied by the hourly wage rate of the absent worker.

Catastrophic costs due to TB: total costs (indirect and direct combined) exceeding a given threshold of the household’s annual income, here defined as exceeding 20%, as recommended by WHO [42].

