## Background

Most people with TB can fully recover from the disease with early diagnosis and treatment. However, it continues to be a leading cause of death worldwide, killing over one million people each year [1–3]. In 2020, an estimated 10 million people developed TB, and 1.4 million died as a result of TB. Of these, more than 87% of the global TB cases were reported in 30 TB high-burden countries [4]. Africa is one of the most affected regions, accounting for one-fourth (25%) of the global TB burden [5]. In Ethiopia, the incidence of TB was 140 cases per 100,000 people in 2020 [6].

The WHO has ambitious targets of a 95% reduction in TB deaths, a 90% reduction in TB incidence, and no catastrophic costs due to TB by 2035 [7]. However, according to a WHO report, approximately 4.1 million people with TB will not have been diagnosed or reported to national authorities by 2021 [8]. Most of these undetected cases were found in low- and middle-income countries or countries with weak healthcare systems. Under-detection of TB cases is also the most common problem in Ethiopia [9–11] with a high magnitude of undiagnosed smear-positive pulmonary TB (PTB) cases found in the community [12]. According to the 2021 national TB prevention and control guideline, one-third of patients with active TB remain undiagnosed and untreated in Ethiopia, and 39% of cases were not reported or not diagnosed in the Amhara region [13].

Although WHO planned to reach zero catastrophic costs, TB still causes financial hardships for the affected families [14]. Although TB medications and laboratory tests are offered free of charge in developing countries, including Ethiopia, the direct and indirect costs associated with TB are still very high [15]. TB patients face a high cost due to charges for health services in private clinics, costs for transport, accommodation, nutrition, and lost income due to the inability to work [16, 17].

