A recent study conducted in Ethiopia showed that more than 70% of the participants sought treatment from traditional or religious healers for a minimum of 6 months before eventually seeking care from the modern healthcare system [28]. The utilization of traditional or religious healers for an extended period before seeking modern healthcare services may have played a significant role in causing delays in diagnosing TB. Thus, integrating traditional TB care with the modern healthcare system may be important to increase case detection, reduce diagnosis delays, and reduce catastrophic costs. Integrating traditional TB care with modern care can also bridge the gap between conventional practices and contemporary medical advancements, fostering a holistic and patient-centric approach to TB management. It may also help to create a more comprehensive, accessible, and patient-friendly TB care system. Figure 1 shows the pathway and contributing factors for the low detection rate, diagnosis delay, and catastrophic cost. While the literature lacks a precise definition of “integrating traditional TB care with modern care,” for the purpose of this study, it is defined as the collaborative effort between traditional care practitioners and modern care practitioners through referral linkage and training.

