### Outcomes of interest

The study will have three outcomes of interest. The primary outcome is the TB case detection rate. The secondary outcomes of interests are diagnosis delay and costs of TB care. The case detection rate will be expressed as percentage. The diagnosis delay will be defined as the time interval between the onset of symptoms and the confirmation of TB diagnosis, which includes patient delay and health system delay. The cost of TB care will include both direct and indirect costs of the patient for TB care and treatment as collected from the patients themselves and their medical records. Direct costs include out-of-pocket payments for medical services (counseling, drugs, laboratory tests, X-rays, and hospital stays) and non-medical services such as transportation, food, and accommodation costs.

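### The one-year case detection rate rises when diagnosis comes earlier, by about 5 points per month of delay removed, even if no additional case is ever found

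*Protocol article*

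**What the plan says.** All references are to the protocol article.

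- **Primary outcome** (Outcomes of interest): "The primary outcome is the TB case detection rate".
- **Definition** (Measurements, repeated in Appendix 2): "The case detection rate will be calculated as the number of cases notified divided by the number of cases estimated for that year".
- **Denominator** (Measurements): an annual rate scaled to the catchment population; "The WHO estimator for the year 2022 was 132 per 100,000".
- **Numerator** (Sample size calculation for TB detection rate): "all cases that are confirmed as TB patients in the selected districts will be considered as the final sample size". On entry, Randomization and recruitment says: "Participants will recruit to the study when confirmed they have any form of TB and are registered to the DOT programs". Neither sets a condition on the date of symptom onset.
- **Timing** (Data collection): "The data will be collected at baseline and at the end of 1 year of the intervention". Table 1 in Appendix 1 runs screening and referral for one year. The months 3 and 6 assessments (Phase 3) are described only as intermediate.
- **Delay** (Outcomes of interest): diagnosis delay, from symptom onset to confirmed diagnosis, is a secondary outcome that the same intervention is meant to shorten.

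**The concern.** The ratio works as a detection measure when delay is stable: cases carried in from earlier onsets roughly balance those carried out to the next year. The intervention is designed to break that balance in one arm. When delay shortens, patients who would have been registered after the year's end are registered within it, while those carried in from before are registered as well. The intervention-arm numerator then draws on more than 12 months of onsets, and the denominator stays at 12.

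This affects the meaning of the main result. The rationale in Background and Discussion is missed cases; Background puts the gap at "39% of cases were not reported or not diagnosed in the Amhara region". A higher primary rate would be read as closing that gap. Part or all of it could instead be the same cases found sooner, which the trial already measures as a secondary outcome, and that part would fade once delay settles at its new level.

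**Working it through.** **Plan's own figures.** The protocol states no target, effect size or power for the case detection rate, so there is no such figure to reproduce. Its only quantified delay effect is a proportion falling from 59.9% to 45.9%. That calculation reproduces: 199 per arm (two-sided 0.05, 80% power, no continuity correction), and 199 × 2 × 1.10 = 437.8, the stated 438. A change in the proportion delayed cannot be converted into months without the delay distribution, which is not given.

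**Inputs**
- CDR0, the rate without intervention: 100% − 39% = 61% (Background). Treating the unreported or undiagnosed share as the complement of the detection rate is an assumption.
- d, the fall in mean delay between the start and end of the year, in months: not in the document, so a range is shown.
- Incidence steady, and the share of cases ever detected unchanged.

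**Formula.** Registrations in the year cover 12 + d months of onsets, so

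rate = CDR0 × (12 + d)/12 = CDR0 × (1 + d/12).

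| d (months) | Rate | Rise (points) |
|---|---|---|
| 0 (control arm) | 61.0% | 0 |
| 0.5 | 63.5% | 2.5 |
| 1 | 66.1% | 5.1 |
| 2 | 71.2% | 10.2 |
| 3 | 76.2% | 15.2 |

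**Simulation check.** Delays are exponential, the hazard of diagnosis changes when screening starts, and the share ever detected is fixed.

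| Mean delay (months) | Year 1 | Year 2 |
|---|---|---|
| 3 to 2 | 66.3% | 60.8% |
| 4 to 2 | 70.9% | 61.2% |
| 6 to 3 | 75.9% | 61.3% |

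The rise matches the formula and is one-off.

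**Scale in counts.** Assume six of the 15 districts and towns, each of average size: 2.6 million × 6/15 = 1.04 million people. Expected cases are 1.04 million × 132/100,000 = 1,373, or 686 per arm, of which 61% is 419. A 3-month cut gives 686 × 0.7625 = 523, or 104 more registrations with no additional case.

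**Is months 7-12 free of the effect?** Only if delay falls at once.
- Exponential delays, mean 6 to 3 months: the excess in months 7-12 is 3 × (e^−2 − e^−4) = 0.35 month of onsets, so the rate is 61 × (1 + 0.35/6) = 64.6%.
- Delay falling linearly by 2.1 months over the year: the excess is constant, so months 7-12 read 61 × (1 + 2.1/12) = 71.7%, the same as the full year.

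**The case against.** **It is a cited standard indicator, and early detection is a stated aim.** Both are true, so cases brought forward are a benefit and should not be dismissed as spurious. But the indicator is being read across a change in delay that the intervention itself causes in one arm. Randomisation does not remove that.

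**The window is inferred.** This stands. The count's start and end dates are not stated. Elsewhere, recruitment ends on September 30, 2022 in one section and December 30, 2023 in another, and the WHO estimate is for 2022 in one section and 2023 in another. If counting began only after delay had settled, the effect would be absent. The one-year screening period and the end-of-year data collection make the first year the natural reading.

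**A later-period analysis may sit in the full protocol or analysis plan.** It may. The point rests on the stated ratio and period, not on that silence.

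**Stronger readings that the documents do not support**
- A reader might take the Background figure, that more than 70% of participants "sought treatment from traditional or religious healers for a minimum of 6 months before eventually seeking care from the modern healthcare system", as the backlog of TB patients at these sites. That gives 0.70 × 6 = 4.2 months and a rate of 82.3%. The sentence describes participants in one cited study and does not say that they were TB patients. The figure also needs screening to reach every one of them.
- A reader might infer that months 7-12 are unbiased. The working shows otherwise when delay falls gradually, which is plausible with the training rounds at months 3 and 6 in Appendix 1.
- A reader might infer that earlier and additional detection can never be separated here. Onset-to-diagnosis time is already an outcome, so much of the needed data is planned.
- A reader might want months 1-6 dropped from the primary claim. That would also discard cases that would never have been found, and halve the counts in a three-versus-three district comparison.

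**Conclusion.** The concern holds in direction and mechanism. As defined, the primary rate rises by about CDR0 × d/12 in the intervention arm when mean delay falls by d months within the measured year, with no additional case ever found. At CDR0 = 61% that is about 5 points per month. The result assumes steady incidence, an unchanged share ever detected, and a count covering the first year of screening. The size for this trial is unknown, because the protocol gives neither a mean delay nor an expected cut in months. A real gain in missed cases may occur as well; the primary rate alone does not show how much of a rise is which. The consequence is a limit on the conclusion, not a reason to replace the outcome.

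**What to change.** 1. State the start and end dates of the count and the year of the WHO estimate, and reconcile the differing dates. Keep the 12-month rate as primary.
2. In both arms, also report the rate by registration quarter and for months 7-12, each against the matching fraction of the annual estimate (one quarter, one half).
3. Beside the 12-month rise, report the part explained by earlier diagnosis: control-arm rate × between-arm difference in mean diagnosis delay (months) / 12, from the onset dates already collected. The formula needs the difference reached by year end, so patients registered in the last quarter are the better source. In the linear example the year's average difference is 2.1/2 = 1.05 months, which would explain only 61 × 1.05/12 = 5.3 points of a 10.7-point rise.
4. Conclude that more cases were detected, and not only the same cases sooner, only if the rise persists in months 7-12 and exceeds that explained part.

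The cost is analysis and reporting text, using registration and onset dates that the trial needs anyway. The later window has a wider interval because it uses about half the registrations. It also keeps some bias if delay falls gradually, which is why both conditions in step 4 are needed.
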